## Abstract

**Background:**

Disorders of consciousness (DOC), i.e., unresponsive wakefulness syndrome (UWS) or vegetative state (VS) and minimally conscious state (MCS), are conditions that can arise from severe brain injury, inducing widespread functional changes. Given the damaging implications resulting from these conditions, there is an increasing need for rehabilitation treatments aimed at enhancing the level of consciousness, the quality of life, and creating new recovery perspectives for the patients. Music may represent an additional rehabilitative tool in contexts where cognition and language are severely compromised, such as among DOC patients. A further type of rehabilitation strategies for DOC patients consists of Non-Invasive Brain Stimulation techniques (NIBS), including transcranial electrical stimulation (tES), affecting neural excitability and promoting brain plasticity.

**Objective:**

We here propose a novel rehabilitation protocol for DOC patients that combines music-based intervention and NIBS in neurological patients. The main objectives are (i) to assess the residual neuroplastic processes in DOC patients exposed to music, (ii) to determine the putative neural modulation and the clinical outcome in DOC patients of non-pharmacological strategies, i.e., tES(control condition), and music stimulation, and (iii) to evaluate the putative positive impact of this intervention on caregiver’s burden and psychological distress.

**Methods:**

This is a randomised cross-over trial in which a total of 30 participants will be randomly allocated to one of three different combinations of conditions: (i) Music only, (ii) tES only (control condition), (iii) Music + tES. The music intervention will consist of listening to an individually tailored playlist including familiar and self-relevant music together with fixed songs; concerning NIBS, tES will be applied for 20 minutes every day, 5 times a week, for two weeks. After these stimulations two weeks of placebo treatments will follow, with sham stimulation combined with noise for other two weeks. The primary outcomes will be clinical, i.e., based on the differences in the scores obtained on the neuropsychological tests, such as Coma Recovery Scale-Revised, and neurophysiological measures as EEG, collected pre-intervention, post-intervention and post-placebo.

**Discussion:**

This study proposes a novel rehabilitation protocol for patients with DOC including a combined intervention of music and NIBS. Considering the need for rigorous longitudinal randomised controlled trials for people with severe brain injury disease, the results of this study will be highly informative for highlighting and implementing the putative beneficial role of music and NIBS in rehabilitation treatments.

**Trial registration:**

ClinicalTrials.gov identifier: NCT05706831, registered on January 30, 2023.

## Introduction

Music is a powerful stimulus affecting human perceptual, cognitive and motor brain functions, including movement, language, memory, attention, and emotions [1]. Musical activities in a clinical setting are highly motivational, as they activate the dopaminergic mesocorticolimbic reward circuitry, allowing for their reiteration over time, which leads to learning and ultimately to brain plasticity [2]. Indeed, a recent meta-analysis of 84 neuroimaging studies using structural magnetic resonance imaging (MRI) and functional MRI (fMRI) evidenced plastic changes in the physiology and anatomy of primary and non-primary sensory areas of the supratemporal lobe as well as cortical and subcortical motor circuits in frontostriatal regions as a consequence of years of musical practice in healthy musicians [3].

The potential role of music for the neurorehabilitation in the realm of severe acquired brain injury (ABI), such as disorders of consciousness (DOC), is still largely unexplored. ABI includes a wide range of conditions caused by traumatic events (e.g., traumatic brain injury), by vascular event (e.g., ischemic or haemorrhagic stroke), or by cerebral anoxia, toxic or metabolic insults (see [4] for a review). These neurological conditions can result in mild to severe impairments of motor and cognitive functions as well as in emotional and neuropsychiatric symptoms, which in turn may lead to a significant level of disabilities and poor functional outcome. Various rehabilitation techniques and treatments have been developed for the neuropsychological deficits associated with ABI (e.g., aphasia, neglect, attention and memory deficits, etc.), ranging from behavioural to cognitive interventions [5]. However, current evidence on rehabilitation techniques of ABI highlights relevant methodological and measurement inconsistencies, mainly due to the heterogeneity of this group of patients. Furthermore, rehabilitation interventions are often very complex and target multiple outcomes, which can be difficult to evaluate independently.

In fact, ABI could result in DOC, which, in turn, based on the observable behavioural features and their inferred relationship to level of consciousness, is clinically manifested as coma, vegetative state (VS), or minimally conscious state (MCS) [6]. Coma is a condition clinically defined as the complete loss of spontaneous or stimulus-induced arousal [7]. This condition is a self-limiting state that typically resolves within 2 weeks and transitions into either VS or MCS [6]. VS is a condition of wakeful unconsciousness, which is diagnosed when spontaneous eye-opening remerges, although the absence of any discernible evidence of language comprehension, verbal or gestural communication, or reproducible purposeful behavioural responses to visual, auditory, tactile or noxious stimuli persist [8]. Lastly, MCS is a condition of severely altered consciousness characterised by minimal yet definite behavioural evidence of self or environmental awareness. It is a condition that usually results from the improvement in consciousness after coma or VS [6].

For the diagnosis of DOC type, the neurologist is typically aided by electroencephalography (EEG), a widely available routinely-used neurophysiological technique that records the synchronised post-synaptic electrical activity of neurons. In DOC patients, EEG signal recorded during rest is clearly atypical; it is indeed characterised by a generalised slowing in the theta or delta ranges and it presents other patterns including epileptiform activity, burst-suppression and alpha-coma. EEG is highly functional for the differentiation of DOC types: for patients without preserved consciousness, EEG shows predominant low, mostly delta, frequency, combined with a marginalization of the higher frequencies, both in terms of the global power of brain activity and in functional connectivity patterns; for MCS patients the opposite EEG pattern is seen: higher frequency bands are preserved both in global power and in functional long-distance connections [9].

Additional to the analysis of oscillatory patterns in the resting-state EEG, also the evoked responses to passive stimulation, typically auditory, have been studied in DOC patients. Among these responses, the one that has biomarker features, meaning it also has some predictive power in relation to the awakening outcome of the patient, is N100. According to a predominant theory of brain function (the Predictive Coding Theory or PCT; [10]), the N100 tackles the predictive process of anticipating the sensory environment based on learning its properties by extracting the events’ statistical probabilities and continuously updating its internal model. In the auditory system, a decreased N1 reveals a memory process which is further modulated by the precision of the context: if a context is uncertain, such as when a listener has never heard a song before, the N1s to all sounds of that song are enhanced as compared to when the tones of the song are learned [10].

Given the clinical and neurophysiological features of DOC patients, music may represent a useful means that could function as an alternative communication channel for multiple reasons. Music represents a nonverbal auditory stimulus with a marked emotional salience (e.g., [11, 12]); as such, it may be regarded as an optimal stimulus in contexts where cognition is severely compromised and stimuli with personal meaning may produce relevant behavioural changes [13–15]. This might be particularly relevant as the most successful rehabilitation interventions are those that are tailored to the individual [16]. Moreover, music-based interventions are based on integrity of the hearing system, which is usually intact in DOC conditions, despite a frequently impaired visual system [17]. Second, music listening may be seen as a kind of enriched sensory stimulation and, hence, a subtype of cognitive rehabilitation strategies; these strategies are based on the idea that an enriched environment benefits brain plasticity and improves recovery of injured brains [18]. Some studies [19, 20] showed as music affect neural networks, accelerating brain plasticity and avoiding sensory deprivation. Multisensory stimulation treatment, based on auditory, visual, tactile, olfactory and gustatory stimuli, can improve the level of consciousness, above all when the stimuli are of high emotional relevance. This aspect is very important also for music stimulation that ought to be used as rehabilitation treatment in DOC.

Neuropsychological studies have shown that music increases arousal and attentions in DOC patients, with significant cortical and Autonomic Nervous System (ANS) activity [21]. Specifically, music accelerates brain plasticity by increasing the activity in frontal, temporal, parietal and subcortical processes, with an important effect on the recovery process [22]. Moreover, in DOC patients, the emotional content of salient music leads to an activation of limbic structures [23, 24], as well as an increase in eye blinks during the exposure to preferred songs [21]. The impact of music on DOC patients is also visible in their EEG responses. O’Kelly et al. [21] investigated the cognitive correlates of music perception in DOC patients and found that passive exposure to preferred songs increased EEG amplitude in frontal midline theta and alpha in both VS and MCS cohorts. These findings resonate with what has been observed even in healthy subjects: the spectral power of the frontal midline theta is increased during listening to preferred pleasant music in contrast to unpleasant music [25]. The salience of reward circuits in DOC is confirmed by the fact that this condition is often associated with widespread impairment of the dopaminergic system, as well as a reduced level of dopamine in the cerebrospinal fluid [26]. Therefore, interventions aimed at stimulating dopamine release may be particularly appropriate for DOC. In fact, a context of preferred music is deemed to be more appropriate than a neutral context to the expression of residual cognitive functioning in patients with DOC [27]. In sum, music-based interventions have consistently been associated with behavioural and neural improvements among DOC patients (for a review, see [28]).

A further group of rehabilitation strategies for brain-lesioned patients, including DOC patients, consists of neuromodulation aimed to alter the physiology of the neural circuits responsible for the behaviour under investigation. Among several neuromodulation approaches, there are pharmacological interventions (e.g., amantadine hydrochloride) [29], deep brain stimulation (for a review see [30]), and Non-Invasive Brain Stimulation techniques (NIBS) [31]. NIBS exists in various forms, although one of the most adopted in clinical settings is transcranial electrical stimulation (tES). This technique consists of delivering a small (1–2 mA) current via two electrodes placed on the scalp. According to the stimulation parameters, tES affects neural excitability and has plastic effects (mediated by NMDA-receptors) [32]. These currents, cathodal (-) or anodal (+), generate an electric field that can modulate spontaneous neural activity by interfering with the membrane potential of the underlying neuronal compartments by inducing, respectively, hyperpolarization (inhibiting effect) or depolarization (facilitating effect) [33]. Importantly, the induced changes become more stable and long-lasting (i.e., aftereffects) when stimulation is repeated several times [34]. Key targets for stimulation in the neurocognitive domain are the dorsolateral prefrontal cortex (DLPFC), especially in working memory, attention, and executive functions, and the posterior parietal cortex (PPC), which plays a critical role in visual spatial perception and attentional processes [35]. Several tES studies show improvements in clinical (e.g., GCS, CRS-R, cognitive, motor) and surrogate (i.e., EEG, TMS, fMRI) outcomes of patients with DOC [36–38], for a review see Kuo et al. [39], although this effect is more evident among MCS patients rather than among unresponsive wakefulness syndrome patients (VS/UWS) [40]. NIBS is, thus, considered a useful tool in the rehabilitation of clinical populations such as patients with DOC [41]; for instance, tES has been used as a potential adjuvant treatment to improve symptoms in patients with hemispatial neglect after stroke [42]. However, there is an increasing understanding that patients do not homogeneously respond to NIBS]. This might be ascribed to the fact that the methodology adopted in tES studies is characterised by a large variability as concerns stimulation parameters, participant characteristics as well as the characteristics of associated rehabilitation treatment.

With this study we propose a novel rehabilitation protocol that combines music-based intervention and NIBS in neurological patients aimed to (i) assess the residual neuroplastic processes existing in DOC state, and (ii) evaluate the putative modulation of these processes by a non-pharmacological 2-weeks intervention combining electric (tES) and auditory (music) stimulation. The musical stimulation will consist of musical pieces that vary in familiarity and complexity (from pieces chosen from the favourite ones for the patient to novel pieces following classical tonal style up to atonal pieces). We hypothesize that tES, altering the physiology of neural circuits, can increase the plastic effect of music stimulation and thus increase the responsiveness of the patient. As far as we know, there are no studies in the literature that have evaluated the effectiveness of the association of these treatments in DOC patients Furthermore, an additional novel aspect will be the use of autobiographical music, hence emotionally relevant to the patients.

In addition, we also want to ascertain the influence of this rehabilitation protocol on caregiver’s burden and psychological distress, since acquired brain injury has an important impact on physical, psychological, social and also financial conditions of caregivers; their entire life is modified in order to take care of the patient, causing a strong emotional burden, with high levels of psychophysiological distress, depression, anxiety and a more complex symptomatology called prolonged grief disorders [43, 44]. In this regard, an aim of this study is to evaluate the caregiver’s psychological burden both before and post rehabilitation treatment in order to assess the effect of music stimulation and brain stimulation also on caregiver’s emotional condition.

The outcome measures will be clinical, namely based on the neurologist’s observations of clinical improvement and responsiveness, measured through specific scales as well as neurophysiologically. For the latter, continuous EEG is expected to display a decrease of power spectra of slow frequency bands (delta-theta) and an increase in power for faster frequency bands (alpha, beta, gamma). We also expect to evaluate residual memory and learning processes in DOC patients by measuring a higher EEG N100 component amplitude after compared to before treatment. Also, amplitudes of the later-stage auditory P2 and latencies of the N100 and P2 will be explored. More broadly, the present intervention combining music exposure with electric neuromodulation is expected to produce increased evoked responses indexed in EEG measures.

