#### Music stimulation

Music stimulation will consist of passive listening to 8 musical tracks. Four tracks will be chosen based on the musical preferences of each patient. Preferences will be derived from a musical anamnesis, namely a structured interview with the caregiver to know the patient’s lifestyle history and musical taste, conducted by the neuropsychologist. The outcome of this interview will help to tailor an individual treatment with familiar and self-relevant music, as previously done [47, 48]. The other four tracks are fixed and chosen by us based on previous literature: Adios Nonino by A. Piazzolla (used in several brain imaging studies); the Prelude in C major by J. S. Bach and the Prelude in C minor from the “Well-tempered Clavier”–I vol.; and a “atonal” version of the C major Prelude (also from the “Well-tempered Clavier”) where the original interval relationships between each note have been altered while maintaining the ascending/descending trend and temporal values of the notes. The two preludes and the atonal version have been used in previous neurophysiological and behavioural studies of auditory memory in healthy and elderly adults [49–52]. For optimising the stimulus variation, the eight tracks will be organized in playlists always alternating based on familiarity (the favourite song alternates a fixed one), on acoustic features (e.g., a track containing lyrics alternates an instrumental one) and emotional content (an arousing track alternates a relaxing one).

All patients will undergo standard physiotherapy rehabilitation treatment, according to the hospital guidelines, for one hour a day, 5 days a week. In addition, most of these patients are treated with specific drug therapy (such as, amantadine, citicoline, dopamine, etc.) in order to increase the level of consciousness. During data analysis these aspects will be considered and treated as necessary. Specifically, drug treatment and doses will be inserted as confounding factors and covariates in the ANOVAs.

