## Discussion

With this trial we present a novel clinical intervention combining music exposure with NIBS in DOC patients, also assessing the impact of this rehabilitation protocol on caregiver’s burden and psychological distress. Both music and NIBS have been largely proven effective in the realm of brain lesions. Nonetheless, this is the first study to propose a clinical protocol including a combined effect of these two intervention strategies among post-coma patients. Further strengths of the current protocol are the sample size and the use of a variety of objective measures, including neurophysiological ones such as EEG, to show the cognitive and functional improvement of DOC patients.

In relation to EEG recorded during music stimulation, our intervention is expected to produce two outcomes. The first consists of increased evoked responses amplitudes to sounds reflecting a residual plasticity of the auditory cortex in DOC patients after the music-based intervention combined with electric stimulation. Second, the continuous EEG is expected to display a decrease of power spectra of slow frequency bands and an increase in power for faster frequency bands. Overall, our ambitious aim of inducing and evaluating beneficial effects of music and brain stimulation on psychological and neurophysiological measures would represent a novel rehabilitation approach, not yet explored in DOC patients.

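### The protocol's own theory has learning lower the N1, but its hypothesis takes a higher N100 after treatment as evidence of memory and learning

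*Protocol article*

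**What the plan says.** The Introduction to the Protocol article gives two accounts of the N1 (also called N100).

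- **Theory.** The paragraph on evoked responses adopts predictive coding and states that "a decreased N1 reveals a memory process which is further modulated by the precision of the context". For a song the listener has never heard, it says that "the N1s to all sounds of that song are enhanced as compared to when the tones of the song are learned".
- **Hypothesis.** The closing paragraph of the Introduction plans to "evaluate residual memory and learning processes in DOC patients by measuring a higher EEG N100 component amplitude after compared to before treatment", and adds that the combined intervention "is expected to produce increased evoked responses indexed in EEG measures". The Discussion repeats the direction and expects "increased evoked responses amplitudes to sounds reflecting a residual plasticity of the auditory cortex in DOC patients".

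The Introduction also gives a second reason to measure this component. Among evoked responses, "the one that has biomarker features, meaning it also has some predictive power in relation to the awakening outcome of the patient, is N100". No direction of change is attached to that statement.

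The section on primary outcomes has the evoked N100 recorded while the patient listens to the morning treatment playlist. Data analysis lists auditory evoked responses among the primary outcomes, averages the EEG around sound onsets in the music, compares amplitudes before and after the intervention, and makes all tests two-sided at 0.05.

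**The concern.** The same construct, memory and learning, is tied to a smaller N1 in one paragraph and to a larger one in another, and no section explains the reversal. A reader holding the result would not know which sign supports the hypothesis. A rise could be presented as learning on the strength of the closing paragraph of the Introduction, and a fall could be presented as learning on the strength of the theory. A primary outcome that can be read as support in either direction does not test the claim made for it.

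The design adds to the problem. The component is measured on the music that serves as treatment, so familiarity with that music changes between the baseline and post-treatment recordings. An overall change in N1 may then mix growing familiarity with any change in the general responsiveness of the auditory system.

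**Working it through.** There is no stated figure to reproduce. The check compares statements and directions.

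1. **Sign under the theory.** The Introduction has N1 larger for unheard music and smaller once the tones are learned. Going from new to learned therefore predicts a decrease.
2. **Sign in the hypothesis.** The closing paragraph of the Introduction names memory and learning and predicts an increase after treatment. The construct is the same and the sign is opposite.
3. **Polarity.** Data analysis describes N1 as a negative potential, so a higher value might mean a less negative one. That reading fails, because both the Introduction ("is expected to produce increased evoked responses indexed in EEG measures") and the Discussion ("increased evoked responses amplitudes to sounds reflecting a residual plasticity of the auditory cortex in DOC patients") predict larger responses.
4. **Does the new-to-learned shift occur here?** Music stimulation specifies eight tracks: four preferred by the patient and four fixed. The aims paragraph of the Introduction describes some of the music as novel. Experimental design and procedures plays music twice a day on weekdays for two weeks: 2 × 5 × 2 = 20 sessions. If the afternoon used other tracks, exposure to the recorded morning playlist would be 2 × 5 × 1 = 10 sessions. In either case, the fixed tracks are heard repeatedly before the post-treatment recording.
5. **What an overall change measures.** Let learning lower N1 amplitude by x and regained responsiveness raise it by y. The overall pre/post change is then y − x.
   - If x = 0, the change is +y: a rise with no learning.
   - If y = 0, the change is −x: a fall that is entirely learning.
   - If x = y, the change is 0, although both processes are present.

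   A rise shows only that y exceeds x. The document gives no value for either, so this shows that offset is possible, not that it occurs.
6. **What a contrast by track type measures.** For the fixed tracks the change is y − x(fixed), and for the preferred tracks it is y − x(preferred). The difference is −(x(fixed) − x(preferred)). The responsiveness term cancels if it is the same for both track types. Where the preferred tracks are already known at baseline, x(preferred) is near 0 and the contrast is close to −x(fixed), which is the sign that the theory predicts.

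**The case against.** The strongest reply is that expecting a larger N100 is coherent with the trial's aims. The stated objective is to assess residual neuroplastic processes, the Discussion reads larger responses as plasticity of the auditory cortex, the N100 is offered as a marker of awakening, and the central hypothesis is about responsiveness. On this view, only the words about memory and learning are misplaced. That largely stands, and it narrows the point: the expected rise can be kept, but its label cannot.

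Two stronger readings are tempting, and the documents support neither.

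- **True learning would be scored as failure.** No success rule is set for N100 and testing is two-sided, so a fall would be tested and could be significant. It would contradict a stated expectation, not fail a criterion.
- **The neuroplasticity objective cannot be answered.** The primary outcomes section assigns that objective to the EEG power spectra, so it does not rest on N1 alone.

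Three further replies hold in part.

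- Data analysis does not say that all eight tracks are averaged together. Pooling is an inference, and the Discussion's claim to separate acoustic from autobiographical effects suggests some analysis by stimulus type. The offset argument therefore applies to an overall comparison, if one is used.
- The preferred tracks are already familiar, so new learning is expected mainly for the fixed ones. This limits how far an overall N1 should fall. It does not turn a rise into evidence of learning.
- An analysis plan that is not shown may fix the averaging. It could not remove the conflict between two statements printed in this article.

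**Conclusion.** The contradiction holds. Under the theory that the protocol adopts, a higher N1 after repeated exposure to the playlist cannot be read as memory or learning, yet the closing paragraph of the Introduction reads it that way for a component of a primary outcome. The consequence is one of interpretation: the sign attached to learning is reversed, a null overall change could hide two opposite effects, and either direction could be claimed as support. No numerical size can be given, because the document states no expected N1 change.

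The conclusion takes the theory paragraph as the protocol's working account and assumes that at least some fixed tracks are new to the patient at baseline. It does not depend on the sample size, the power calculation or how the tracks are pooled.

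**What to change.** Before analysis, reconcile the theory and hypothesis paragraphs of the Introduction with Data analysis and the Discussion.

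1. Label an overall N1 increase as auditory responsiveness or residual plasticity, and state that it will not be interpreted as memory or learning.
2. If learning is to be inferred from N1, pre-specify a decrease as the predicted direction. Test it as the pre-to-post change in N1 to the initially novel fixed tracks relative to the change for the preferred tracks. The musical interview with the caregiver could also record whether any fixed track was already known.

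A single-session difference between the atonal version and the C major Prelude may look like a ready-made learning index, because the atonal version was built as one "where the original interval relationships between each note have been altered while maintaining the ascending/descending trend and temporal values of the notes". It is a poor one. Both are fixed tracks with the same exposure, so learning common to both is subtracted out, and what remains largely reflects their different interval structure.

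The cost is rewording and splitting already recorded epochs by track type. The estimate will be noisier. With N epochs shared equally between the four fixed and four preferred tracks, and noise variance s² per epoch, the overall mean has variance s²/N. The difference between the two halves has variance s²/(N/2) + s²/(N/2) = 4s²/N, so the epoch-noise standard error doubles. Stable acoustic differences between tracks largely drop out of the pre-to-post change. The contrast still assumes that responsiveness affects both track types alike. That may fail if preferred music is more arousing, and it should be stated as a limitation.
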